#### Microwave ablation

MWA involves localised destruction of the tumour using heat generated by microwave [17–19]. For the treatment of liver lesions, it is usually carried out as a short-stay procedure under general anaesthesia as with RFA, although it can also be performed under local anaesthesia in some patients [17]. As with RFA, multiple sessions may be required in some patients to treat all the lesions (index disease). It is usually performed percutaneously under image guidance (usually ultrasound scan) [17]. It is more effective than RFA in lesions near large blood vessels [17–19]. Major technical limitations of MWA include low power, shaft heating, large diameter probes, long and relatively thin (1–2 cm) ablation zones, and unpredictability regarding the size and shape of the zone of ablation [17].

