#### Comparison of methods of thermal ablation

Non-randomised studies comparing MWA with RFA suggested that MWA is better than RFA in terms of technical feasibility and lower disease recurrence in patients with unresectable CLM [25]. Of the newer forms of ablative methods, such as HIFU, CyberKnife®, and cryotherapy, there are no publications comparing these newer ablation methods with either RFA or MWA. In reality, different surgeons and radiologists have their own preferences of method of ablation because of this uncertainty.

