#### Inclusion/exclusion criteria

Inclusion criteriaAge ≥ 18 yearsAble to provide written informed consentMDT diagnosis of colorectal liver metastases considered to be resectable or ablatable with curative intentResected colorectal primary or plan for primary resection with curative intentMeets *one or more* of the following criteria:Considered high-risk for surgery due to age (based on local policy)Major co-morbidities as judged by the treating clinician. Examples include history of myocardial infarction, severe chronic airway disease, major cerebrovascular accidents (CVA), pulmonary embolism (PE)Liver metastases with poor prognosis and high-risk surgery due to tumour burdenExamples include extensive synchronous disease, need for two stage resection or ALPPS, small anticipated remnant liver volume, curable extra-hepatic disease, downstaged with chemotherapy, poor response after chemotherapy but still resectable or ablatableSuitable candidate for either liver resection surgery or thermal ablation as judged by the MDTAble and willing to comply with the terms of the protocol including health-related quality of life (HRQoL) questionnaires

Exclusion criteriaIncurable extra-hepatic metastasesNot a suitable candidate for liver resection surgeryNot a suitable candidate for thermal ablationConcurrent malignant disease (except basal cell carcinoma)Patients who have undergone previous surgery or ablation for CLMPlanned simultaneous resection of primary and liver metastasesPregnancy

All patients will provide written informed consent. Patients will then be randomised on a 1:1 basis to receive either thermal ablation or surgical resection. A computer-generated minimisation programme that incorporates a random element will be used to ensure treatment groups are well-balanced for the following participant characteristics:Research siteSynchronous/metachronous diseasePrimary cancer in situ (Yes/No)High-risk for surgery due to age (Yes/No)Major co-morbidity (Yes/No)Poor prognosis or high-risk surgery due to tumour burden (Yes/No)Largest lesion size ≤ 5 cm (Yes/No) [13]Planned surgical resectionOpenLaparoscopicPlanned ablative treatmentRFAMWA

Blinding will not be performed.

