### Intervention: thermal ablation (RFA or MWA)

#### Definition of the intervention in the ablation arm

For patients in the ablation arm, the intervention is defined as the collection of ablation sessions conducted as treatment for the index disease (as defined above). Either RFA or MWA will be carried out according to the local availability of equipment and expertise. Ablation may also be performed at laparoscopic or open surgery if the percutaneous approach is contraindicated. Minimum standards for delivery of ablation to be achieved during the trial will be agreed by all centres in a pre-trial standardisation meeting.

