### Control: surgery

#### Definition of the intervention in the surgical resection arm

For patients in the surgical arm, the intervention is defined as the collection of operations conducted as treatment for the index disease (as defined above). Liver resection will be carried out as per centre protocol. The majority of patients will have undergone resection of the primary cancer. Patients may be offered open or laparoscopic liver resection depending on site and stage of disease. In selected cases, the liver first approach may be considered. Procedures for patients with extensive metastatic disease will include two-stage liver resection, venous embolisation or the ALPPS procedure (Associated Liver Partition and Portal vein ligation for Staged hepatectomy). Minimum surgical outcomes to be achieved during the trial will be agreed by all centres in a pre-trial standardisation meeting.

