### Data analysis

#### Statistical analysis

Analysis and reporting will be in line with CONSORT guidelines. Analyses will be carried out on both an intention-to-treat (ITT) basis and per-protocol (PP) basis. Non-inferiority hypotheses will be tested at the one-sided 2.5% level of significance. Superiority hypotheses will be tested at the two-sided 5% level of significance. 95% confidence intervals for parameter estimates will also be reported.

The primary analysis will assess the difference in DFS. The non-inferiority hypothesis will be tested using an appropriate survival model to incorporate random effects with respect to research site and including adjustment for the stratification factors. The specific survival model that is most ‘appropriate’ cannot be determined a priori; for example, the Cox proportional hazards model will be considered but will not be used if the proportional hazards assumption is violated. Patients for whom an event is not reported during their trial follow-up will be censored at the last date that they were known to not have had an event.

Differences in rates such as complication rates and recurrence rates will be analysed using multi-level logistic regression incorporating random effects with respect to research site and will include adjustment for the stratification factors.

Subgroup analysis based on the type of surgery (open or laparoscopic liver resection) and type of ablation (RFA or MWA) will be performed. If there are truly substantial differences in efficacy between types of treatment within an arm, then these subgroup analyses, while likely having limited precision, will give an unbiased indication of the magnitude and direction of the differences. This will allow us to explore how the treatment effect partitions into these more precise components, which will allow us to assess the validity of assumption that there is no substantial difference in efficacy between open and laparoscopic surgery, and there is no substantial difference between RFA and MWA. This will also allow us to perform sensitivity analyses using imputation methods to assess the impact of changing the proportion of each type of treatment performed within arm on the primary treatment effect estimate. This will facilitate the generalisability of our inferences to wider practice and to potential changes in the uptake of each type of treatment over time.

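### The within-arm contrasts of RFA with MWA and of open with laparoscopic resection are called unbiased, although the type of procedure is not randomised

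*Protocol article*

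**What the plan says.** Under Statistical analysis, the protocol article plans subgroup analyses by open or laparoscopic resection and by RFA or MWA. The quantity of interest is introduced with "If there are truly substantial differences in efficacy between types of treatment within an arm", and the text continues that "these subgroup analyses, while likely having limited precision, will give an unbiased indication of the magnitude and direction of the differences". The results are to serve two purposes: to judge the assumption that the types within each arm do not differ substantially, and to allow imputation-based sensitivity analyses showing how the primary treatment effect would change under another mix of types. The second purpose is meant to support generalisability.

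Other sections say how type comes about:

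- Inclusion/exclusion criteria: "Patients will then be randomised on a 1:1 basis to receive either thermal ablation or surgical resection". Planned resection type and planned ablation type are both minimisation factors.
- Definition of the intervention in the ablation arm: "Either RFA or MWA will be carried out according to the local availability of equipment and expertise".
- Comparison of methods of thermal ablation: "different surgeons and radiologists have their own preferences of method of ablation because of this uncertainty".
- Definition of the intervention in the surgical resection arm: "Patients may be offered open or laparoscopic liver resection depending on site and stage of disease".

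**The concern.** Randomisation protects the comparison of ablation with resection. It gives no protection to a comparison of RFA with MWA, or of open with laparoscopic surgery, among patients of one arm. The article itself names the drivers of type as centre, operator and disease. For the surgical approach the driver includes stage, which is prognostic, so this is confounding by indication in the plan's own terms. The only limitation the article attaches to these contrasts is precision. That concerns variance; more patients would narrow the interval around the wrong value.

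At stake is the interpretation of two secondary analyses. Differences in who receives each technique could be reported as differences between techniques, and then carried into statements about how the trial result would look under another mix of procedures.

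**Working it through.** **1. What is randomised and what is not.** Set against each other, the sections listed above leave one randomised factor (ablation or resection) and two chosen ones. Minimisation on planned type balances the arms within each planned type. It does not allocate the type.

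**2. What adjustment can reach.** The primary and rate models carry random site effects and the stratification factors. The minimisation list holds site, synchronous or metachronous disease, primary in situ, age risk, co-morbidity, tumour-burden risk, largest lesion up to 5 cm, and the two planned types. Lesion location and number of lesions are not on it. Location may steer the choice: the Microwave ablation section says of MWA that "It is more effective than RFA in lesions near large blood vessels". In any centre that uses only one modality, type is also largely inseparable from site.

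**3. Event counts, from the plan's own sample size.** Inputs from Sample size calculations: 14 months' DFS with resection, a 4-month margin, 80% power, one-sided 2.5%, 4-year accrual, 2-year follow-up, 5% drop-out. Assumptions made here: 14 months is a median, times are exponential, and the margin is a hazard ratio of 14/10 = 1.4.

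- Events: 4 × (1.960 + 0.842)² / (ln 1.4)² = 278.
- Probability of an event with 48 months' uniform accrual and 24 months after the last patient: 0.884. Then 278 / 0.884 = 315, and 315 / 0.95 = 332, which agrees with the stated 330.
- Probability of an event with 24 months per patient: 1 − 2^(−24/14) = 0.695.
- Events per arm: 165 × 0.95 = 156.75 patients; × 0.884 = 138.5 (about 139); × 0.695 = 109.

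**4. Precision of a 50:50 within-arm contrast.** SE(log HR) = 2/√events.

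- 138.5 events: SE 0.170; 95% CI factor e^(1.96 × 0.170) ≈ 1.40.
- 109 events: SE 0.192; 95% CI factor e^(1.96 × 0.192) ≈ 1.46.

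**5. Illustration of the bias.** The article gives neither the type mix nor any imbalance, so these inputs are assumed: no true difference between types, and one unadjusted binary factor with hazard ratio h, present in 60% of one type and 30% of the other. The apparent hazard ratio is approximately [1 + 0.6(h − 1)] / [1 + 0.3(h − 1)].

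- h = 1.5: 1.30/1.15 = 1.13.
- h = 2.0: 1.60/1.30 = 1.23.

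On the log scale these are 0.123 and 0.208, or 0.123/0.192 = 0.6 to 0.208/0.170 = 1.2 standard errors. Over other imbalances, the same formula gives 1.08 (60% versus 40%, h = 1.5) to 1.31 (70% versus 30%, h = 2.0). Simulated exponential times gave the same two values, and 1.00 with equal prevalence.

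**6. Carry-over to the change of mix.** Suppose the true ablation-to-resection hazard ratio is 1.0, the trial mix in one arm is 50:50, and the reweighting is log-linear. The article names only imputation methods, so the last is an assumption. Moving that arm wholly to the seemingly better type shifts the hazard ratio by half the log bias, away from 1.0 to 1/√1.13 = 0.94 or 1/√1.23 = 0.90 if the arm is ablation. The true value is unchanged.

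**The case against.** Four points can be made for the plan.

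- **The primary analysis is untouched.** A reader might infer that confounded contrasts alter the primary effect. The article does not support that: the change of mix is a sensitivity analysis, and the non-inferiority test and its estimate stand as they are. This objection holds in full and limits the weight of the point.
- **Centre and disease are partly adjusted for.** Site, tumour burden and lesion size are minimisation factors. This holds in part. The article does not repeat the adjustment for the subgroup analyses, and adjustment reduces confounding without making a chosen exposure unbiased.
- **Planned type may already be intended.** The article speaks of partitioning the treatment effect into components, which could mean effects by planned type, and an analysis plan would normally settle that. However, the sentence in question is about types within an arm, and the later text is about treatment performed. On either definition, a comparison between types is not randomised.
- **The illustrated bias is smaller than the confidence interval, and low precision is admitted.** This is true for 1.13 to 1.23 against factors of 1.40 to 1.46. A shift of 0.6 to 1.2 standard errors is still systematic, and the interval does not allow for it.

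A further inference to avoid is that using planned type yields a randomised comparison of techniques. It yields a randomised comparison of ablation with resection within each planned type. Why those effects differ between planned types remains an observational question.

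**Conclusion.** The point holds. The article claims a property, absence of bias, that its design does not give to RFA versus MWA or to open versus laparoscopic resection within an arm. The conclusion rests on the article's own account of how type is chosen and does not depend on any figure above.

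The size is unknown, because the documents give no type mix or imbalance. The spurious hazard ratio of 1.13 to 1.23 is an illustration under assumed inputs, and adjustment would make it smaller to the extent that it captures the factor. The confidence interval factor runs from 1.40 (139 events per arm) to 1.46 (109 events per arm, 24 months per patient).

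The error should be corrected because it governs what the technique comparison and the generalisability analysis may claim. It does not threaten the primary result or the sample size.

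**What to change.** 1. Delete the word unbiased and state that type within an arm is not randomised.
2. Define the subgroups by the planned type recorded before randomisation. As minimisation factors, planned resection type and planned ablation type should be available for patients in both arms.
3. Within each planned-type stratum, estimate ablation versus resection with a confidence interval, and report the treatment-by-planned-type interaction.
4. Base the change-of-mix sensitivity analysis on those stratum effects, and state its assumption: differences between strata are due to technique and not to centre or patient selection.
5. Report within-arm contrasts by type received only as adjusted, observational and descriptive.

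The cost is wording in the protocol and analysis plan and a little more analysis work. No new data are needed and the sample size does not change. The downside is that the technique comparison carries a weaker claim, which is the claim the design supports.

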### When can one consider ablation to be equivalent to liver resection in terms of long-term results?

Liver resection for CLM is a major surgical procedure and carries a postoperative mortality of approximately 3–4% and a complication rate of ~ 40% [31]. Because of the effects of major surgery and the associated pain, the patients take about 2–3 months to recover from surgery and the quality of life is only 0.65 on a scale of 0 to 1 (1 indicating perfect health) even six months after liver resection [25]. As the patient group identified for this trial are those considered high-risk in terms of age, co-morbidity and the extent of liver resection required, the mortality, morbidity and length of hospital stay are likely to be considerably higher than the average and the health-related quality of life and recovery period significantly greater.

In contrast, the ablative methods have fewer complications (6%) [26] and the quality of life is 0.74 (on a scale of 0 to 1) by three months [25]. An informal discussion with patient representatives from Bowel Cancer UK suggested they were willing to trade-off 3–6 months (average 4 months) of their long-term survival in return for a less-invasive procedure with significantly lower complication rates compared to surgery. So, on average, the long-term results of ablation and surgery can be considered equivalent if the difference in long-term survival between the modalities is < 4 months. Clearly, if ablation results in similar or better survival, ablation is the better option since it is less invasive and results in better quality of life in the short-term.

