### Sample size calculations

A total of 330 patients are required to demonstrate non-inferiority (non-inferiority margin of four months) of thermal ablation with respect to resection in terms of DFS with 80% power at the 2.5% one-sided level of significance, allowing for a four-year accrual period, two-year follow-up, and assuming 14 months DFS in the resection arm and allowing for a 5% drop-out rate.

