### Participant-completed questionnaires

Participant-completed questionnaires measuring quality of life (EQ-5D, EORTC QLQ-C30, EORTC LMC21) will be completed in clinic at baseline (following consent but before randomisation) and at 3, 6, 12, 18 and 24 months post randomisation. Patient-completed questionnaires measuring health and social care resource use will be completed at 3, 6, 12, 18 and 24 months post randomisation.

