#### Secondary outcomes

Overall survival, defined as time from randomisation to death (any cause), evaluated at two and five yearsLocal, regional and extra-hepatic/systemic recurrence of disease at two years post randomisation (as defined above)DFS (measured from end of intervention) at two years post randomisation (as defined above)Use of subsequent therapies within two years post randomisation after treatment failure, for example, use of additional radiofrequency ablation or surgery for recurrence in either armHealth-related quality of life (EQ-5D, EORTC QLQ-C30, EORTC LMC21) [37–39] at baseline, and 3, 6, 12, 18 and 24 months post randomisationComplications during treatmentPost-treatment complications using Clavien-Dindo classification system [40, 41]Length of intensive therapy unit (ITU) and inpatient stay (length of hospital related to treatment or treatment-related complications) at 30 days and 3 months after completion of treatment

Outcomes related to health economics and qualitative research are reported under the health economics section and qualitative research.

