Continuous measures such as length of ITU and hospital stay will be analysed using multi-level normal-errors regression incorporating random effects with respect to research site and including adjustment for the stratification factors. In the case of deviation from the Normality assumptions, the appropriately transformed variable will be analysed.

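### The covariates printed for continuous outcomes include no baseline score, so the quality-of-life comparison as written gives up precision that the collected baseline forms could supply

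*Protocol article*

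**What the plan says.** The Statistical analysis section of the protocol article assigns models by type of outcome: a survival model for disease-free survival (DFS), multi-level logistic regression for rates, and one model for continuous outcomes. The last is introduced by "Continuous measures such as length of ITU and hospital stay" and is given as "multi-level normal-errors regression incorporating random effects with respect to research site and including adjustment for the stratification factors". Lengths of stay are its only named examples.

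Under Inclusion/exclusion criteria, "A computer-generated minimisation programme that incorporates a random element will be used", followed by the balancing factors: site, timing of metastases, primary in situ, the three high-risk reasons, lesion size, planned type of resection and planned type of ablation. None is a quality-of-life score.

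Secondary outcomes lists EQ-5D, EORTC QLQ-C30 and EORTC LMC21 "at baseline, and 3, 6, 12, 18 and 24 months post" randomisation. Participant-completed questionnaires says that these forms "will be completed in clinic at baseline (following consent but before randomisation"). Outside the Statistical analysis section, EQ-5D is modelled only in the Health economic analysis, as the input to QALYs.

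**The concern.** A patient's own baseline score is usually among the strongest predictors of the later score on the same scale. The trial collects it before allocation is known, which matters because treatment is unblinded. Yet the printed covariates do not include it. An analysis plan that followed the sentence literally would compare quality of life with wider confidence intervals than the data allow.

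The comparison matters to how the trial will be read. The section on when ablation can be considered equivalent to resection argues that some survival may be traded for an easier treatment. It reports that after ablation "the quality of life is 0.74 (on a scale of 0 to 1) by three months", against 0.65 six months after resection. If ablation proves non-inferior on DFS, the size and precision of the quality-of-life difference will shape the interpretation, although no decision rule depends on it.

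**Working it through.** **Does the rule reach quality of life?** Among the secondary outcomes, overall survival, recurrence, DFS from end of intervention, subsequent therapies and complications are times to event, rates or counts. What remains as continuous is length of stay and the quality-of-life scales. The continuous-outcome sentence gives stays as examples, not as a closed list, and no other between-arm model is offered. The natural reading is that it covers the scales, though it does not say so.

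**The plan's own figures.** The article states no power or target difference for quality of life. Its only sample-size calculation is for DFS, at "80% power at the 2.5% one-sided level of significance". Treat 14 months as an exponential median and the margin as 14 against 10 months, a hazard ratio of 14/10 = 1.4. Then 4(1.960 + 0.842)²/(ln 1.4)² gives 278 events. With an event probability of 0.884 (uniform 48-month accrual, follow-up to 24 months after the last entry), 278/0.884 is about 315, and dividing by 0.95 for drop-out gives 332 on those assumptions, against 330 stated. This bears on the present point only by supplying 165 patients per arm.

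**Inputs for quality of life**
- n = 165 per arm (Participants section).
- Two-sided 5% test: "Superiority hypotheses will be tested at the two-sided 5% level of significance".
- Correlation r between baseline and follow-up score: not in the article; assumed 0.3 to 0.7.
- Equal SD in both arms; differences expressed in SD units.

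**Formulas**
- Variance of the arm difference without baseline: 2/n. With baseline as a covariate: 2(1 − r²)/n.
- Ratio of unadjusted to adjusted variance: 1/(1 − r²). It does not depend on n.
- Difference detectable at 80% power: (1.960 + 0.842) × √[2(1 − r²)/n]. With r = 0 this is 2.802 × √(2/165) = 2.802 × 0.110 = 0.308 SD.

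| r | 1 − r² | Variance ratio | SE ratio | Detectable difference with baseline (SD) | Power at 0.308 SD |
|---|---|---|---|---|---|
| 0 (no baseline term) | 1.00 | 1.00 | 1.00 | 0.308 | 80% |
| 0.3 | 0.91 | 1.10 | 1.05 | 0.294 | 83.6% |
| 0.5 | 0.75 | 1.33 | 1.15 | 0.267 | 89.9% |
| 0.7 | 0.51 | 1.96 | 1.40 | 0.220 | 97.5% |

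Put the other way, baseline adjustment lowers the variance by 9%, 25% or 49%. With fewer forms the pattern is the same. At 156 per arm (165 × 0.95, rounded down) the detectable difference falls from 0.317 to 0.275 SD at r = 0.5. At an assumed 110 per arm it falls from 0.378 to 0.327 SD.

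These are upper figures. The formulas ignore site and the stratification factors; in so far as those already carry the information in the baseline score, the gain is smaller.

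**Is chance imbalance a second loss?** With 165 per arm, the baseline difference between arms has a standard deviation of √(2/165) = 0.110 SD. The share carried into an unadjusted follow-up comparison is r times that: 0.033, 0.055 or 0.077 SD. At r = 0.5, the adjusted variance is 0.75 × 2/165 = 0.00909 and the carried part is 0.25 × 2/165 = 0.00303. Their sum is 0.01212 = 2/165, the whole unadjusted variance. The imbalance is therefore already inside the wider interval.

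**The case against.** The strongest reply is that the article never says what a quick reader might infer, namely that quality of life is compared on follow-up scores alone with adjustment limited to the listed factors. The sentence does not close its covariate list and does not name quality of life. Its examples are stays, which have no baseline value. It has no patient or visit level, so it is not a complete model for a scale measured at five follow-up visits. The outcome definition itself includes the baseline assessment, so using that value as a covariate, or as part of a repeated response, is compatible with the text. A full protocol or analysis plan, not shown, may specify it.

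Most of this stands, and it rules out calling the plan wrong or the baseline score excluded. It does not remove the point. The article chose to print a covariate set for a class of outcomes to which these scales naturally belong, and a better set is already in hand.

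A second tempting reading is that omitting baseline biases the comparison, or adds a harm beyond the wider interval. It does neither. Over repeated randomisation the unadjusted difference is unbiased, and the decomposition above shows that imbalance and lost precision are the same variance.

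It is also fair to say that the size rests wholly on an assumed correlation. At 0.3 the gain is small.

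**Conclusion.** The point holds as a minor one. If the continuous-outcome rule is applied to the quality-of-life scales as printed, the variance of each arm difference is up to 1.10, 1.33 or 1.96 times what baseline adjustment would give, at assumed correlations of 0.3, 0.5 and 0.7, less whatever the stratification factors already explain. This rests on reading the rule as covering those scales, on the assumed correlations, and on baseline forms being available for nearly all patients. The documents do not support saying that the plan forbids baseline adjustment or that its quality-of-life estimates would be biased. The primary DFS analysis, its non-inferiority test and the sample size of 330 are untouched.

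**What to change.** Add a sentence to the continuous-outcome rule, or to the analysis plan if it is not already there: each quality-of-life score (every EORTC scale and the EQ-5D score) is analysed with the patient's own baseline value of that score as a covariate, in addition to site and the stratification factors. Settle it before outcome data are seen, so that the covariate cannot look chosen after the fact.

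How the five follow-up visits are modelled together and how missing baseline scores are handled can be left to the analysis plan. For EQ-5D, that plan should say how its rule sits beside the multiple imputation already foreseen in the Health economic analysis. Length-of-stay models need no change. The cost is a sentence and one extra model term, with no new patients, visits or forms.
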